**Topics in the training programme for health visitors**
• Current evidence-based knowledge about breastfeeding, including:
- Anatomy of the breast and physiology of lactation
- Preparing for breastfeeding
- Breastfeeding positions
- Suckling technique
- Alleviating breastfeeding problems, for example by strengthening parents’ action competence
- Breastfeeding as a joint parenting task
- The social context of the parents and its’ influence on breastfeeding
• Tailoring communication
• Breastfeeding self-efficacy – how to improve and support parents’ self-efficacy
**Objective of the parental breastfeeding programme**
To support parents who want to breastfeed in establishing effective breastfeeding by improving health visitors’ and parents' breastfeeding knowledge, and enhancing parents’ self-efficacy, and action competency through a focus on four simple key principles and tailored information
**Content of the parental breastfeeding programme**
The programme consists of four key principles:
• Skin-to-skin contact as much as possible during the first week while the mother and father are awake [43]
• Frequent breastfeeding defined as a minimum of eight times including identifying the infant’s cues for being ready for breastfeeding and signs of getting enough milk [44, 45]
• Proper positioning of the mother-infant dyad including introducing the parents to laid-back breastfeeding and focus on the mothers’ experience of pain and relaxation as guidelines for positional changes [46, 47]
• Acknowledgment of the mother and the father as equal parents with different roles in relation to breastfeeding [48]
The parents’ breastfeeding self-efficacy and breastfeeding knowledge is intended to be supported by the communication based on Bandura’s theory of self-efficacy and the related four sources to increase self-efficacy: 1) Mastery experiences, 2) Vicarious experience, 3) Social persuasion, and 4) Emotional arousal [42]. Kreuter’s theory of tailoring knowledge to the specific needs of the individual [49] is furthermore included to address findings from the needs assessment [30]
Supportive health educational materials include:
• A dialogue sheet
• A pamphlet with visuals for the changes in colour of a healthy infants’ stool during the first week
• A postcard with the four key principles
• A website with written knowledge, videos, podcasts, a quiz about breastfeeding aimed at preparing parents for breastfeeding, and furthermore a trouble shooting guide

Should families decline further visits by the health visitor, they will no longer receive the intervention. The investigators will make no efforts to retain the families in the study.

##### Intensified intervention

In the intervention arm, families in which the mothers are younger than 25 years when they give birth (young age) and/or have primary school or vocational training as their highest educational attainment (low education) are offered an intensified intervention following the same breastfeeding principles, but they will receive a higher dose of the intervention. The aim is for health visitors to be proactive in delivering support and preventing breastfeeding cessation in this group, which carries an increased risk of early cessation. The intensified intervention is delivered within the first five months through additional follow-up phone calls (*n* = 7) and a single extra visit, all of which are scheduled to occur in-between the home visits (see details in Additional File 1). If a mother receiving follow-up by telephone ceases breastfeeding, she will no longer receive the telephone follow-up. Families accepting the intensified intervention are free to decline further extra telephone calls and/or visits.

The intervention is expected to reach > 6,000 families in the trial period, of whom 30–40% are expected to be in the target group for the intensified intervention. After the trial period, health visitors in the control clusters will receive the training and supportive materials developed during the intervention.

Figure 2 presents the programme theory in a logic model structure. The programme theory guides evaluation by outlining our hypothesis as to which mechanisms drive intended changes in outputs and outcomes to be measured, e.g., the hypothesis that the breastfeeding support programme will promote frequent breastfeeding, which will increase the likelihood of establishing effective breastfeeding, among others because milk production is stimulated causing sufficient milk to reach the infant, which, in turn, is hypothesised to lower the risk of readmissions.

**Fig. 2 Fig2:**
[figure not shown]
Programme theory of the Breastfeeding Trial

#### Randomisation

The participating municipalities were randomised for either the intervention or control arm by a statistician using computer-generated cluster randomisation. Randomisation was stratified by Danish region and number of annual births per municipality (0 =  < 900, 1 = 900 +). The number of annual births in a municipality was associated with maternal educational level and age as urban cities with more inhabitants and thus more births had fewer mothers with a low educational level and young age than rural districts with fewer births. Stratification of randomisation was performed to increase the exchangeability of the two trial arms.

The intervention works by strengthening competencies at health visitor level. Once achieved, such competencies are difficult and unethical not to use, wherefore randomisation at the level of families was discarded. Randomising at the cluster level serves to mitigate the risk of contamination between trial arms. Allocation to the intervention or the control arm is based on address and municipal affiliation.

### Outcome measures of the effectiveness trial

Data on the primary outcome measure of exclusive breastfeeding at four months are collected through a survey. To gain as much insight into the intervention mechanisms and effects as possible, we collect data from various sources as described in the aim. As the trial was designed to show effects on survey-based measures, we elaborate on the survey trial design below and afterwards describe the supplementary data sources.

### Survey data

The primary outcome measure is studied by using self-reported measures collected via self-administered web-based questionnaires. Survey questionnaires are distributed via emails to mothers recruited via the health visiting programme at the following five postpartum time-points: one week, one month, four months, six months and 12 months. Additionally, fathers/partners were invited to a survey at one month postpartum (see Fig. 3 for an overview timeline). From the surveys, we also study a range of secondary outcome measures.

**Fig. 3 Fig3:**
[figure not shown]
Overview of the survey study questionnaire distribution

#### Primary outcome measure

Proportion of mothers who exclusively breastfeed at four months postpartum.

#### Secondary outcome measures

The secondary objectives are to assess the effectiveness of the breastfeeding support programme on:Duration of exclusive breastfeeding (continuous)Infant readmissions to hospital related to nutritionMothers’ experiences of breastfeeding problemsParental trust in the health visitorMaternal breastfeeding self-efficacyPaternal feeling of inclusion in the breastfeeding supportBreastfeeding in mothers with overweight

### Sample size and power calculations

For sample size calculation, an estimated eight clusters in each arm were used, totalling 16 clusters. Expected participation rate was 80% with 30% attrition from the first questionnaire at one week postpartum to the third questionnaire at four months postpartum. A power calculation was made using breastfeeding frequencies from 2016 made available from The National Child Health Register [50]. The ambition was to raise the proportion of women breastfeeding at four months in the intervention clusters to the national level. In the design phase, we obtained data on the mean prevalence of breastfeeding at four months in the project regions (49%) and at national levels (56%) in 2016 from the National Child Health Register. The observed difference in the proportion of women exclusively breastfeeding for a minimum of four months corresponds to an odds ratio of 1.32. In the power calculations, an interclass correlation coefficient (ICC) of 0.001, as observed in the previous intervention study [27], was used. Reaching a statistical power of 80% with a 5% significance level is thus achievable provided data are collected from 111 mothers in each cluster. In each cluster, the sample size was extended to ensure that a minimum of 52 mothers were young or had low educational attainment. This yields a power of 80% to investigate an increase in exclusive breastfeeding at four months from 45 to 55% in this subgroup.

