### Study population

The study setting includes 21 municipalities in Denmark, all of which are situated in the North Denmark Region (*n* = 6) or Region of Southern Denmark (*n* = 15) (see Fig. 1). Denmark consists of a total of five regions. The two selected regions have some of the highest proportions of mothers who are of young age and/or have a low educational attainment. Each of the 21 participating municipalities constitutes a cluster in the trial.

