**Development and implementation**
For the adaptation of the previous successful breastfeeding intervention done by Nilsson and colleagues (2017) in hospital setting, an assessment of the needs of families following discharge from hospital after birth and until six months postpartum was carried out. Programme objectives corresponding to findings from the needs assessment formed the basis of the adaptation. In the adaptation process, a participatory approach including health visitor representatives from each of the intervention municipalities was chosen to enhance ownership, to match the organisational structure of the setting (the Danish Health visiting programme), and to ensure implementation in the intervention municipalities. The final intervention programme consisted of a breastfeeding programme for parents and a related training programme for health visitors. In December 2021, 210 health visitors from the 11 intervention municipalities completed a preparatory 3.5-h e-learning course, and in March 2022 they participated in the 15-h physical attendance interactive training programme supported by a written manual. Following training, the health visitors immediately initiated implementation of the programme in their municipalities

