### Statistical methods

We use random allocation to remove any influence of both measured and unmeasured variables on treatment allocation. Before conducting regression analyses, descriptive statistics will be applied to assess selection into the trial, baseline equivalence of trial arms and loss to follow-up.

Regression analyses will be applied when analysing primary outcomes. We will account for the clustered nature of data by using random effects models for binary and continuous outcomes [51] and shared frailty models for analysing time-to-event and recurrent events in continuous outcomes [52]. Intention-to-treat analyses will be conducted. These analyses will include all mother-infant dyads in the relevant trial arms irrespective of their compliance or loss to follow-up. Complete-case analyses will be conducted restricted to observations with available outcome measures [53]. For the intention-to-treat analyses, the survey data will be linked to the Danish national registers including all births; and missing outcome data will be handled by inverse probability weighting and missing covariates by multiple imputation from the registers. The probability weights will be estimated by conducting logistic regressions with outcome data (yes vs. no) as dependent variable and the following baseline variables as predictors: maternal educational, maternal age, cohabitation status, partner’s education, household income, occupational status, maternal smoking status, maternal BMI, and maternal as well as paternal psychiatric histories.

The effect of the intensified intervention will be examined by including an interaction term between treatment arms and a binary indicator of the mother being young or having low educational attainment.

All models will be analysed with treatment alone and adjusted for known predictors for breastfeeding duration collected in the survey (smoking status, maternal age, maternal education, parity, mode of delivery, maternal BMI and cohabitation status) and for design variables used in the randomisation (region of Denmark and number of annual births (< 900 births/year vs. ≥ 900 births/year). As the randomisation will hopefully have distributed the characteristics evenly between trial arms, these adjustments are made to increase the robustness of the effect estimations. Missing predictors will be imputed using multiple imputations and the results compared to the complete case analysis.

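### Power is stated for 16 clusters and one ICC from a hospital study; restate it for the 11 and 10 municipalities randomised, over a range of municipal ICCs

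*Protocol article*

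**What the plan says.** The section on sample size and power gives the design input as "an estimated eight clusters in each arm were used, totalling 16 clusters". The effect comes from the 2016 register figures, the "mean prevalence of breastfeeding at four months in the project regions (49%) and at national levels (56%) in 2016", and the difference "corresponds to an odds ratio of 1.32". For clustering, "an interclass correlation coefficient (ICC) of 0.001, as observed in the previous intervention study [27], was used". The Background places that earlier study in hospitals. The result is 80% power at the 5% level with 111 mothers with data per cluster. The section then says that cluster sizes were extended so that each has at least 52 mothers who are young or have low education. It does not give the resulting cluster size.

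Elsewhere the article describes a larger trial. Study population: "Each of the 21 participating municipalities constitutes a cluster in the trial". Table 2, under development and implementation: "210 health visitors from the 11 intervention municipalities completed a preparatory 3.5-h e-learning course". That leaves 21 − 11 = 10 control municipalities.

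On differences between municipalities, the Randomisation section notes that "urban cities with more inhabitants and thus more births had fewer mothers with a low educational level and young age than rural districts". Under Statistical methods, "All models will be analysed with treatment alone and adjusted for known predictors for breastfeeding duration collected in the survey", and also for region and births stratum. A municipality's own earlier breastfeeding rate is not in that list. The difference-in-difference section plans to retrieve register data on all mother–child dyads in the 21 municipalities from 2015 onwards.

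**The concern.** The article's only power figure belongs to a design with five fewer clusters than were randomised, and no figure is given for 11 versus 10.

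The clustering input also comes from a different kind of cluster. An ICC of 0.001 at a 49% rate means that true municipal rates vary with a standard deviation of only 1.6 percentage points. The article itself says that municipalities differ in maternal age and education, and its Background names both as predictors of early cessation. Neither statement gives a municipal ICC, but together they make 0.001 a value to be checked rather than carried over.

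With 21 clusters, between-cluster variance soon dominates the standard error, and more mothers per cluster help less and less. If the municipal ICC is several times 0.001, power for the 7-point difference could be well below the stated 80%, and the article would give no sign of it.

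**Working it through.** **Inputs from the article.** Proportions 0.49 and 0.56; ICC 0.001; 8 clusters per arm in the calculation; 11 and 10 in the trial; 111 mothers per cluster; subgroup minimum 52 per cluster (45% vs 55%); subgroup share 30–40% (stated for families reached by the intervention). The 5% level is taken as two-sided, which reproduces the figures. **Assumptions.** Equal cluster sizes; every ICC above 0.001.

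**1. The plan's own figures.**
- Odds ratio: (0.56/0.44)/(0.49/0.51) = 1.32, as stated.
- Without clustering, the pooled two-proportion formula gives n = 798 per arm. With design effect 1 + (m − 1)·ICC and k clusters per arm, m = n(1 − ICC)/(k − n·ICC) = 798 × 0.999/(8 − 0.798) = 110.7, so 111, as stated.
- Subgroup: n = 392, m = 392 × 0.999/(8 − 0.392) = 51.5, so 52, as stated.

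**2. Which approximation.** For 8 + 8 clusters of 111, the design effect is 1 + 110 × 0.001 = 1.11 and the effective n is 8 × 111/1.11 = 800 per arm. SE = √[(0.49·0.51 + 0.56·0.44)/800] = 0.0249, and 0.07/SE = 2.81. Power is 80.2% with normal quantiles (80.1% with the pooled variance) and 74.3% with a noncentral t on 14 df, where 130 per cluster would be needed for 80%. So 111 fits a normal approximation. This is inferred, because the article names no formula.

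**3. The trial as randomised, plan's ICC.** For 11 + 10 clusters of 111, effective n is 1,100 and 1,000, SE = 0.0218 and 0.07/SE = 3.22. Power is 89.5% (normal) and 86.2% (t, 19 df). By t, 93 mothers per cluster would give 80%.

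**4. Extended cluster size.** 52/0.40 = 130 and 52/0.30 = 173.

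**5. Range of ICCs, 11 + 10 clusters, t with 19 df.** Between-municipality SD = √(ICC × 0.49 × 0.51).

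| ICC | SD (points) | 111 per cluster | 130 | 173 |
|---|---|---|---|---|
| 0.001 (plan) | 1.6 | 86.2% | 90.5% | 95.9% |
| 0.003 (assumed) | 2.7 | 79.6% | 84.0% | 90.3% |
| 0.005 (assumed) | 3.5 | 73.3% | 77.4% | 83.7% |
| 0.01 (assumed) | 5.0 | 60.2% | 63.3% | 68.2% |
| 0.02 (assumed) | 7.1 | 43.6% | 45.2% | 47.8% |

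Power falls below 80% at an ICC of about 0.0029 (111 per cluster), 0.0042 (130) or 0.0061 (173).

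**6. Value of the earlier municipal rate.** Suppose it explained half the between-cluster variance at ICC 0.01 (an assumption). The residual ICC is then about 0.005, with 18 df after one is spent. At 111 per cluster, power rises from 60% to 73%.

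**The case against.** The strongest reply is that nothing in the calculation is miscalculated. The odds ratio, 111 and 52 all reproduce, and the article calls the cluster number an estimate. That stands. A reader might infer that the power statement describes no analysis the trial will run. The article does not support this: the outcome, contrast, significance level and allowance for clustering are the trial's own, and only the cluster count is out of date. A reader might also take the 74% for 16 clusters with t quantiles as showing the trial to be underpowered. It does not, because that trial is not being run and 21 clusters give 86% or more on the plan's ICC.

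A second reply is that larger ICCs are speculative. This stands in part. The article gives no municipal ICC. The 7-point gap between the project regions and the country is a difference between means and says nothing about spread among the 21 municipalities. The age and education differences are the stated reason for stratifying on births, and the adjusted model includes age, education, region and births stratum, so the ICC relevant to that model is the residual one. But the stated power allows for no covariates, and ICCs of about 0.003 to 0.006 are enough to bring power below 80%.

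Third, leaving out the earlier municipal rate is a missed gain in precision, not an error, and the register analysis will use pre-programme data in any case. Which of the unadjusted and adjusted models is primary may properly be settled in an analysis plan that is not shown, so no point is made of it.

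**Conclusion.** The point holds in a limited form. The published 80% belongs to 16 clusters, an ICC from a hospital study and, by inference, normal quantiles. For the 21 municipalities randomised, the plan's own ICC gives a better figure: 86% at 111 mothers per cluster, and about 90–96% at the extended size.

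That figure is fragile to an input the article does not examine. At the extended size, power is 77–84% if the ICC is 0.005, 63–68% at 0.01 and 45–48% at 0.02. These ICCs are assumptions, so the trial has not been shown to be underpowered; what the article shows is that its power is not established for municipalities. The 130–173 range rests on applying the 30–40% share to every cluster. Unequal cluster sizes would lower all the figures somewhat.

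**What to change.** 1. Restate power for 11 versus 10 municipalities at the cluster size actually targeted after the subgroup extension, with a small-sample correction (for example t with 19 df). Estimate the ICC from the municipal four-month rates in the National Child Health Register, the source already used for 49% and 56%, and show a range such as 0.001 to 0.02.
2. Add each municipality's pre-programme register rate to the adjusted model as a cluster-level covariate, beside region and births stratum. The register data are already to be retrieved for the difference-in-difference analysis.

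The cost is a recalculation and a few lines in the analysis plan. The covariate uses one cluster-level degree of freedom, and the restated power may be less favourable than 80%. No extra mothers and no change to recruitment are needed. Register data for the trial years are expected in early 2025 at the earliest, but the ICC and the covariate need only pre-programme years.

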### Recruitment to the survey

The health visitors will recruit the families during their first visit after birth. Health visitors have been instructed to inform about the project verbally and in writing in families where the mother meets the eligibility criteria (see information sheet in Appendix A). Enrolment is done by the health visitors who collect families’ consent and help fill in the families’ information in a secure electronic recruitment form. Furthermore, the health visitor assesses whether the mothers qualify for the intensified intervention based on her age and educational level. Participation in the survey and the intensified intervention are independent, i.e., mothers declining participation in the survey may still accept the intensified intervention.

Municipalities will stop recruiting when the required number of mothers with data from the first three questionnaires has been reached, as outlined in the description of the sample size calculation.

### Data collection

The data collection period commenced on 26 April 2022, in both trial arms. From mid-June it has been possible to assess the full intervention in the intervention clusters, including monitoring the effect achieved by introducing breastfeeding counselling in the pregnancy visit. Local variations will exist in the duration of data collection due to a varying number of births in the clusters. Data collection is projected to end by October 2023 in the municipalities with fewest births.

The questionnaires are distributed to families via personal emails and followed up by two reminders sent by text message (SMS).

Mothers for whom reading and filling out a questionnaire are very challenging are offered a phone call or Microsoft Teams call by a project student assistant who will help them complete the questionnaire. At recruitment, the mother will decide whether to accept or decline this offer.

An overview of the data collection timeline is given in Fig. 3, and Table 3 shows which outcomes and covariates are collected from each survey wave.

**Table 3 Tab3:** Overview of quantitative data collection, source and timepoints

Outcome measures	Survey data						Register data
*Sources*	**Mother**					Partner	
Time point since birth (PP)	One week	One month	Four months	Six months	Twelve months	One month	
